**Screening, consent and baseline information**	
Phone screener	Inclusion and exclusion eligibility criteria completed over the phone
Dichotomous Choice Screen	Demonstration of a reliable yes/no response
Count 1–20	Inclusion criteria
Parent/caregiver consent	Required for minors
Child assent	Obtained *via* tablet using participant’s preferred communication method
Baseline questionnaire	Socio-demographic information, basic health and development information, and condition related information (for children with cerebral palsy)
**Neuropsychological assessment tools**	
The Peabody Picture Vocabulary Test (PPVT-5)	Receptive vocabulary
Matrix Reasoning - a subtest from: Wechsler Preschool and Primary Scale of Intelligence, Fourth Edition: Australian and New Zealand Standardised Edition (WPPSI-IV A&NZ) **OR** Wechsler Intelligence Scale for Children, Fifth Edition: Australian and New Zealand Standardised Edition (WISC-V A&NZ)	Perceptual reasoning
Barking (age 5–7 years and 11 months) **OR** Vigil (age 8–15 years and 11 months) Subtests from the Test of Everyday Attention for Children 2 (TEA-ch2)	Sustained auditory attention
Tower of Hanoi (TOH)	Executive functioning including planning and problem solving
Self-Ordered Point Task (SOPT)	Visuospatial working memory
The Motor Free Visual Perception Test-4 (MVPT-4)	Visual perception
**Other standardised measures**	
Wong Baker FACES^®^ Pain Rating Scale Revised (FPS-R)	Current pain intensity score
National Aeronautics and Space Administration Task Load Index measure (NASA-TLX)	Measure of mental, physical, temporal, and overall task difficulty
The System Usability Scale (SUS)	Measure of useability and user satisfaction
**Assessor measure**	
Assessor questionnaire	Completed for each participant by the assessor. Includes quantitative and qualitative information regarding assessment duration, perceived assessment accuracy and challenges faced during administration

### Study instruments and measures

#### Primary outcome measures

The proposed assessment tools assess the cognitive domains of receptive vocabulary, fluid reasoning, attention, executive function, working memory and visual perception. These assessment tools were selected based on best available evidence, are not timed and have features that were appropriate for modification for assistive technology access (e.g., multiple choice response options).

*The Peabody Picture Vocabulary Test*, (*PPVT-5*; Dunn, 2019) will be used to measure receptive vocabulary. It provides an estimate of verbal intelligence (Dunn, 2019) for people aged 2:6–90 years. The PPVT-5 is typically used in populations with suspected speech or reading problems, for people with English as a second language, or where verbal abilities are unknown. Whilst research has demonstrated effective modification of PPVT-III, further research investigating the validity of the revised tool in a sample of people with cerebral palsy reliant on assistive technologies is necessary (Warschausky et al., 2012). The PPVT is a highly recommended supplemental instrument in the U.S. National Institutes of Health Cerebral Palsy Common Data Elements.

*The Matrix Reasoning* subtest of the *Wechsler Preschool and Primary Scale of Intelligence*, *Fourth Edition: Australian and New Zealand Standardised Edition* (*WPPSI-IV A&NZ*; Wechsler, 2012) and the *Wechsler Intelligence Scale for Children*, *Fifth Edition: Australian and New Zealand Standardised Edition* (*WISC-V A&NZ*; Raiford et al., 2016) will be used to measure fluid reasoning. WISC-V A&NZ is an international gold standard measure of intelligence for children. The Matrix reasoning subtest of the WISC-V and WPPSI-IV specifically lends themselves to discrete choice-based accommodation that allow for switch access responses. All others require manual dexterity, timed responses, or complex verbal responses which are inappropriate for accommodations.

*The ‘Barking’* (age 5–7 years and 11 months) and *‘Vigil’* (age 8–15 years and 11 months) subtests of the *Test of Everyday Attention for Children* 2 (*TEA-ch2*; Manly et al., 1998) will be used to assess the child’s ability to sustain their attention. The TEA-ch2 is a standardised, norm referenced assessment tool to measure the attentional capacity of children aged 5-16 years. Dimensions of attention are assessed *via* a number of different subtests (Evans and Preston, 2011).

The *Tower of Hanoi* (*TOH*) will be used to assess executive functions such as problem solving, planning, set shifting and mental flexibility. Traditionally developed for adult populations with neurological impairment, the TOH has since been accommodated as a measure of executive functioning for both children and infants (Welsh et al., 1991; Klahr and Robinson. 1981). In the task, the participant is shown 2, 3 and 4 disc puzzles on 3 rods. Participants are required to re-arrange the disks so that their 3 rods look identical to the examiner’s target rods, following a set of rules and completing the task in as few moves as possible (Welsh et al., 1991). The psychometric properties of the TOH have been examined extensively, with various target displays and scoring rubrics reported. Whilst reported psychometric properties vary considerably across studies (Bishop et al., 2001), it is generally considered an acceptable measure of executive functioning for children (Bull et al., 2004; Anderson et al., 2010).

The *Self-Ordered Point Task* (*SOPT*), developed by Petrides and Milner (1982) will be used to assess visuospatial working memory. Here, participants are shown sets of 6, 8, 10 and 12 abstract images (Strauss et al., 2006). The same images are shown over as many pages as there are images in the set, but the images change location on each page. Participants are instructed to touch a different picture on each page. There are 3 trials for each set, increasing cognitive load as participants are required to recall which pictures have been touched on each trial. Whilst a less commonly used measure of working memory, this is one of the few working memory tasks with psychometric evidence to support its use (Ross et al., 2007), which can be accommodated for eye-gaze and switch access technologies.; results are not time dependent.

The *Motor Free Visual Perception Test-4* (*MVPT-4*; Colarusso and Hammill, 2015) will be used to assess visual perception. The MVPT-4 is a standardised norm-referenced assessment tool for children and adults aged 4 years or older (Colarusso and Hammill, 2015). As a forced choice matching task, the MVPT-4 does not require motor responses, and is appropriate for accommodations for children who use eye-gaze and/or switch access technology to communicate. The normative data is reportedly representative of the US population, and it has shown good content and construct validity (Brown and Peres, 2018) and excellent test–retest reliability (Chiu et al., 2022).

Permission to make accessibility accomodations to copyrighted measures, for the purposes of this research project, has been sought.

#### Secondary/covariate measures

*The Wong Baker FACES® Pain Rating Scale Revised* (*FPS-R*; Wong et al., 1996) will be used to measure pain. The FPS-R is a pain measurement tool made up of 6 pictures of faces numbered 0–10 ranging from “no pain” to “worst pain imaginable.” It was originally created to help children communicate their pain and is now used internationally. Permission to use the FPS-R for this project has been granted.

*The National Aeronautics and Space Administration Task Load Index measure* (*NASA-TLX*; Hart and Staveland, 1988) will be used to evaluate task difficulty. The NASA-TLX measures mental, physical and temporal demand as well as performance, effort and frustration on a 21-point scale, comprised of 7 markers. Low, medium and high rankings comprise each marker.

*The System Usability Scale* (*SUS*; Lewis, 2018) will be used to evaluate user satisfaction. The questionnaire consists of 10 usability items. For each of the 10 items, the participant’s usability of the technology with the assistive device will be assessed using a 10-point scale.

*A Baseline Questionnaire* has been designed to gain some basic socio-demographic information such as age, Socio-Economic Indexes for Areas (*SEIFA*), cognitive testing in the last 12 months, and health/development related information, such as gestational age at birth, level of education, developmental difficulties, vision, and hearing ability. For children with cerebral palsy, condition specific information is also collected using: Gross Motor Function Classification System Expanded and Revised (GMFCS E&R; Palisano et al., 2007), Manual Ability Classification System (MACS; Eliasson et al., 2006), Communication Function Classification System (CFCS; Hidecker n.d.) Viking Speech Scale (VSS; Pennington et al., 2013), and Eating and Drinking Ability Classification System (EDACS; Sellers et al., 2014). Type of computer access method (switch or eye-gaze control technology), individual technology settings, and how long they have used the technology will also be recorded for children with cerebral palsy.

*An Administrator questionnaire* has been designed to gather a description from the assessor on their subjective experience of further improvements in regards to the technical set up and accessibility of the assessment battery for the individual participant. The assessor will also record the number of sessions it took to administer the assessment battery and assessment completion time for each participant.

### Equipment

*Switch access* is an assistive technology which replaces the need to use a computer keyboard or a mouse. The switch can be utilised with a row-column presentation format for forced choice (Figure 3).

*Tobii PCEye mini eye-gaze control technology* involves a specialised video camera mounted below the tablet PC which tracks the user’s eyes. Sophisticated image-processing software in the tablet continually analyses the camera’s image of the eye and determines where the user is looking on the screen (Tobiidynavox, 2016). To select a target the person holds their eye-gaze for a certain time, referred to as ‘dwell’ (Figure 4). If a participant with cerebral palsy is used to a different brand of eye-gaze control technology device, and can be moved across to the study computer, that device can be used if that is the choice of the participant, as there are subtle differences between devices and theirs might be the best fit for their gaze control.

To enable our assessment tools to be switch and eye-gaze control technology accessible on a Window based platform, five of the six assessment tools were accommodated using Grid 3 software (Thinksmartbox, 2018). The tablet to be used in this study will be a Surface Pro 4.29 × 20 cm. Participants will sit approximately 80 cm from the screen. Standard administration of TEA-Ch-2 does not require accommodation. However, a page in Grid 3 was developed with numbers 1–20 randomly placed on the display for the participant to provide the response. The screen will not be displayed until after each trial.

Grid 3 is a software solution which is designed for people with complex communication and or access needs. It includes features which enables the user to control the computer and their environment with a switch, eye-gaze control technology and other assistive technology access solutions.

The assessment tools were accommodated to display the test items as they would be presented in the paper version according to each test manual. However, three communication buttons will also be presented on each screen. This will enable participants to confirm their response selection, or let the test administrator know if they accidently select the wrong answer (perhaps due to eye-gaze or switch control anomalies) or are unsure about the selection. This additional confirmation step is necessary to remove the likelihood of false negatives and positives, and allow some qualitative communication throughout assessment to reduce frustration and maintain rapport. Two additional buttons to navigate to the next and previous page will also be available at the bottom of the screen and will only be accessible to the administrator.

**Figure 3 fig3:**
[figure not shown]
Switch assess.

**Figure 4 fig4:**
[figure not shown]
Eye-gaze control technology.

### Data processing and analysis

Data analysis will be conducted using SPSS v. 25 (Statistical Package Social Science, S.F.W, 2018) and R v 4.1.0 (R Core Team, 2021). Raw scores on standardised assessment tools will be converted to scaled scores and/or standard scores where appropriate. Raw scores on the TOH and SOPT will be converted to z-scores using available published data. Descriptive statistics will be used to summarise demographic and clinical characteristics, assessment tool performance, secondary outcomes, and user experience. Prior to undertaking any statistical analysis, the normality of the scaled/standardised scores and Z-scores for the six assessments tool will be assessed overall and for each combination of administration and access method (i.e., standard administration and switch; standard administration and eye gaze control technology; person with cerebral palsy using switch; and person with cerebral palsy using eye-gaze control technology) using Shapiro-Wilks assessment and visual inspection of histograms.

The measurement agreement and validity of the accommodated assessment tools will be investigated by testing hypotheses of equivalence between scores from the standard administration and scores from the accommodated administration of the assessments. These hypotheses will be tested using paired t-tests for Wilcoxon signed-rank tests if the data is not normally distributed. The significance level for these tests will be adjusted to account for multiplicity and control the overall Type I error rate at 5%. Correlations will be investigated between performances on each of the six assessments for all combinations of access methods, and intraclass correlation coefficients (ICC) will be calculated. For the sample of children without cerebral palsy, the sample size will be sufficient to examine Bland Altman plots for further evidence of measurement agreement and test bias. In addition, we will compare the bivariate correlation matrices with adaptive test scores to examine the nomothetic spans of instruments by comparing coefficients using Fisher’s r to z transformations. Regression models will be investigated to examine between group differences in (i) children with cerebral palsy using switch and eye-gaze control technologies for each of the six assessment tools and for the two user experience measures, and (ii) between typically developing children’s and children with cerebral palsy’s performance using switch and eye-gaze control technologies, across all six assessment tools. Potential confounders and effect modifiers will be investigated for these regression models Associations between test results and secondary outcomes for the children with cerebral palsy will be investigated using chi-squared or Fisher’s exact tests.

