### Primary aims and hypotheses

Aim 1. Examine the psychometric properties (measurement agreement and validity) of accommodated assessment tools by comparing the performance of typically developing children on six cognitive assessment tools administered *via* standardised versus accommodated (switch or eye-gaze control) administration.

*Hypothesis 1-1*: The two types of accommodated instruments (switch or eye-gaze control) will yield standard scores that are not statistically significantly different from standardized administration counterparts.

*Hypothesis 1-2*: Accommodated instruments will demonstrate intraclass correlation indexes of agreement with standard counterparts that would be at least 0.75 (Lee et al., 1989).

*Hypothesis 1-3*: Bland Altman plots will provide further evidence of measurement agreement and test bias, with *a priori* criteria of an acceptable upper 95% confidence limit and lower 95% confidence limit of 1.96 SD of the differences between the methods as equal to or smaller than the normative standard deviation (SD = 15; Bland and Altman, 1986).

Aim 2. Describe and compare the performance and user experience of children with cerebral palsy on six accommodated cognitive assessments administered *via* switch or eye-gaze control technologies.

*Hypothesis 2-1*: Group differences (typically developing, cerebral palsy) in the nomothetic span of test scores computed as within-group bivariate correlation matrices, will not be statistically significant.

*Hypothesis 2-2*: Within the group with cerebral palsy, the access method (switch, eye-gaze) will not result in significant differences in the nomothetic spans of test scores.

*Hypothesis 2-3*: Within the group with cerebral palsy, access method (switch, eye-gaze) will not have a significant effect on user experience as indicated by personal ratings of task difficulty and satisfaction.

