### Sample size calculations

With the proposed sample size of 80 typically developing children and 38 children with cerebral palsy the study will have power of 80% at 5% overall significance to identify equivalence between the assessment administration methods for all six cognitive assessments, allowing for a 10% drop out rate in the group with cerebral palsy who may require more than one assessment session. This calculation assumes an acceptable difference between standard and modified administration methods of up to 1.25 standard deviations. This sample size will give the study power to correctly detect statistical equivalence between the administration methods in the presence of up to 0.4 standard deviations of variation between standard and modified administration scores on average, which may arise due to a learning effect from repeated assessments or the unfamiliarity of typically developing children with eye gaze or switch technology. Statistical Package Social Science (SPSS v.25) (Statistical Package Social Science, S.F.W, 2018) Sample Power 3 and R (v 4.1.0) (R Core Team, 2021) were used for the power computation.

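### Hypothesis 1-1 and its tests carry no equivalence margin, although the study is powered for equivalence within 1.25 SD

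*Protocol article*

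**What the plan says.** Three places in the protocol article bear on the comparison of standard with accommodated administration in typically developing children.

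- **Sample size calculations.** The claim is that "the study will have power of 80% at 5% overall significance to identify equivalence between the assessment administration methods for all six cognitive assessments". The margin follows: "This calculation assumes an acceptable difference between standard and modified administration methods of up to 1.25 standard deviations". Power is said to hold "in the presence of up to 0.4 standard deviations of variation between standard and modified administration scores on average", a shift put down to learning or to unfamiliar technology.
- **Primary aims and hypotheses, Hypothesis 1-1.** Accommodated instruments "will yield standard scores that are not statistically significantly different from standardized administration counterparts".
- **Data processing and analysis.** The stated purpose is "testing hypotheses of equivalence between scores from the standard administration and scores from the accommodated administration of the assessments". The method is then given: "These hypotheses will be tested using paired t-tests for Wilcoxon signed-rank tests if the data is not normally distributed" (the word between the two tests is presumably meant as *or*). On multiplicity: "The significance level for these tests will be adjusted to account for multiplicity and control the overall Type I error rate at 5" per cent. Before any testing, "the normality of the scaled/standardised scores and Z-scores for the six assessments tool will be assessed overall". The same check is planned within subgroups defined by how the test is given and which technology is used.

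The 1.25 SD margin appears only in the sample size section. Hypotheses 1-2 (ICC of at least 0.75) and 1-3 (1.96 SD of the differences no larger than 15) are further, separate criteria for Aim 1.

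**The concern.** The power statement and the decision rule describe different tests. An equivalence test has a null that the difference is at least as large as the margin, and rejecting it supports equivalence. The named tests have a null of zero difference. Failing to reject that null may mean the difference is small, or only that the data are too few or too noisy.

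Two things follow if the text is applied as written. First, the incentives run backwards: losing data or lowering alpha makes Hypothesis 1-1 easier to meet. The Type I error being held at 5% is then a false claim of difference, not a false claim of equivalence. Second, with adequate data the rule can fail a tool for a shift that the sample size section expects and accepts. Hypothesis 1-1 is the first criterion for whether accommodated scores can stand in for standard ones, so its decision rule matters.

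**Working it through.** **Inputs from the protocol article.** Margin 1.25 SD; tolerated true difference 0.4 SD; 80 typically developing children, assigned to switch or eye-gaze; overall alpha 5%; normative SD 15.

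**Assumptions.** The article gives no within-child correlation r, no number of tests and no split by access method. I take r from 0 to 0.87; alpha per test of 5%, 5%/6 (six tools) and 5%/12 (six tools by two access methods); and n = 80 pairs if pooled or 40 per access method. The margin is read in units of the score SD.

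**Step 1: the stated 80% power.** It cannot be reproduced uniquely, because the correlation, the alpha split and the comparison powered are not given. It does fit margin-based calculations. Two-sample two one-sided tests (TOST) at 5% need 18 per group, 36 in all, and 36/0.9 = 40. With 40 per group at 0.025/12, power is 79.8%. The figure is not shown to be wrong, and it points to a margin-based test.

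**Step 2: the correlation implied by Hypothesis 1-3.** If 1.96 × SD of differences = 15, the SD of differences is 15/1.96 = 7.65. With equal SDs of 15, SD of differences = 15√(2(1−r)), so r = 1 − 7.65²/(2 × 225) = 0.87.

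**Step 3: the rule as written.** For a true difference of d score SDs, the paired t statistic is noncentral t with n−1 degrees of freedom and noncentrality d√n / √(2(1−r)). For d = 0.4, n = 80, r = 0.75 this is 0.4 × 8.944 / 0.707 = 5.06, against a two-sided critical value of 1.99 at 5% and 2.95 at 5%/12.

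Chance that the test is significant, so that Hypothesis 1-1 fails:

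| True difference | n | r | 5% | 5%/6 | 5%/12 |
|---|---|---|---|---|---|
| 0.4 SD | 80 | 0.75 | 99.9% | 99.0% | 98.0% |
| 0.4 SD | 80 | 0.5 | 94% | 81% | 73% |
| 0.4 SD | 40 | 0.75 | 94% | 78% | 70% |
| 0.4 SD | 40 | 0.5 | 69% | 41% | 32% |
| 0.4 SD | 40 | 0 | 41% | 18% | 12% |
| 0.4 SD | 20 | 0.75 | 67% | 37% | 27% |
| 0.2 SD (3 points) | 80 | 0.87 | 93% | 79% | 71% |

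Every row lies inside the 1.25 SD margin, so each entry is the chance of failing a tool that the plan counts as equivalent. Reading across, a stricter alpha makes success easier. At r = 0.75, so does having fewer children (80, then 40, then 20).

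**Step 4: false equivalence at the margin.** With a true difference of 1.25 SD and n = 40, the worst case tried (r = 0, alpha 5%/12) gives non-significance in 0.8% of studies.

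**Step 5: a margin-based test on the same data.** TOST power per test, margin 1.25 SD, true difference 0.4 SD, n = 40, one-sided alpha:

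| r | 5% | 5%/6 | 5%/12 |
|---|---|---|---|
| 0 | 98.2% | 89.7% | 83.9% |
| 0.5 | >99.9% | 99.7% | 99.4% |
| 0.75 | about 100% | about 100% | about 100% |

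Here a stricter alpha makes the claim harder, as it should. These are powers for one test, not for all six jointly.

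**The case against.** **The authors may intend TOST.** The analysis section speaks of hypotheses of equivalence, TOST is built from one-sided t-tests, the sample size section states a margin, and a condensed article may leave the mechanics to a fuller plan. On that reading the multiplicity adjustment is also right. This is plausible, but it does not clear the text. Hypothesis 1-1 states its success rule outright as the absence of a significant difference. A plan using TOST would contradict that hypothesis, and a plan following the hypothesis would contradict the sample size section.

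**A reader might infer that biased tools will be passed as equivalent.** With n = 40 and r = 0.75, a 0.3 SD bias (4.5 points) is non-significant 26%, 53% and 63% of the time at 5%, 5%/6 and 5%/12. But 0.3 SD is well inside the plan's own margin, and TOST at 1.25 SD would pass it about 100% of the time. A difference as large as the margin is rarely missed (Step 4). The documents do not support this as the main harm.

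**A reader might also infer that Aim 1 can succeed without evidence of agreement.** It cannot, since Hypotheses 1-2 and 1-3 require positive evidence. At r = 0.75 and SD 15 the SD of differences is 10.6 and 1.96 × 10.6 = 20.8, so the 0.3 SD example would be expected to fail the 15-point limit. Those criteria do not repair Hypothesis 1-1, but they confine the problem to it.

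**The normality check is a small matter.** The article lists scores, whereas a paired test depends on the within-child differences. With 40 to 80 pairs the choice of test should have little effect.

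**Conclusion.** The point holds for Hypothesis 1-1. Its success rule and the named tests omit the margin on which the power claim rests, so hypothesis, analysis and sample size section must be reconciled. The mismatch is in the text and needs no assumption.

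The size of the consequence does rest on assumptions. At 80 pairs and r = 0.75, the 0.4 SD shift that the study is powered to tolerate would fail Hypothesis 1-1 in about 98% to over 99% of studies. At r = 0.87, the value implied by Hypothesis 1-3, a 3-point shift would fail it 71% to 93% of the time, depending on alpha. With 40 pairs or a lower correlation, failure is less frequent, but only because the test has less information; that is the same defect seen from the other side.

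**What to change.** - Reword Hypothesis 1-1 and the matching sentences in the analysis section. For each tool and access method, equivalence is claimed only if TOST on the within-child differences rejects both one-sided nulls; in other words, the matching confidence interval for the mean difference lies wholly within the pre-stated margin.
- State that margin in the hypothesis and in the analysis section, identical to the one in the sample size section, and name the SD it is measured in.
- Apply the multiplicity adjustment to the TOST p-values, so that it controls false claims of equivalence.
- Assess normality on the within-child differences. If they are non-normal, use a Wilcoxon-based interval against the same margin.

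The cost is the wording of one hypothesis and one analysis paragraph. The data and the planned sample are unchanged. With 40 pairs, power per test is about 84% to 100% for r from 0 to 0.75, even at 5%/12.

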### Secondary aims

Describe the completion rates and time to complete assessments of participants in each group.Within the group with cerebral palsy, examine the effects of condition-specific characteristics (type of cerebral palsy, functional levels, and pain) and demographics (age, socio-demographic) on participation.

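### Associations between test results and secondary outcomes in the children with cerebral palsy are assigned only to chi-squared or Fisher's exact tests, although the test results are continuous scores, so scores must be categorised in a group of about 40

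*Protocol article*

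**What the plan says.** **The method.** The Data processing and analysis section states: "Associations between test results and secondary outcomes for the children with cerebral palsy will be investigated using chi-squared" or Fisher's exact tests. It offers no alternative for these associations.

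**The test results.** Earlier in that section: "Raw scores on standardised assessment tools will be converted to scaled scores and/or standard scores where appropriate". For the two tools without standard norms: "Raw scores on the TOH and SOPT will be converted to z-scores using available published data". Normality of all six is to be checked before analysis, so the authors treat them as continuous.

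**The secondary measures.** Under Secondary/covariate measures, pain is a rating: "The FPS-R is a pain measurement tool made up of 6 pictures of faces numbered 0–10". Task load covers dimensions including "performance, effort and frustration on a 21-point scale". Usability items are rated on a 10-point scale. The assessor also records "assessment completion time for each participant". Five functional classification systems give ordered levels.

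**The aim.** Within the cerebral palsy group, secondary aim 2 is to "examine the effects of condition-specific characteristics" (type, functional level, pain) and of demographics on participation.

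**The group size.** It is 40 under Recruitment and 38 under Sample size calculations.

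**The concern.** Chi-squared and Fisher's exact tests compare counts in categories. One side of every planned association is a test result, and all six test results are scores. Following the sentence therefore means cutting each score into groups and treating all children within a group as alike. Where the other variable is pain, task load, usability or time, it must be cut as well, or analysed as many sparse categories.

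The sentence is also out of step with the rest of its section, which uses paired tests, correlations, intraclass correlations and regression for the same scores. The regressions do not cover the gap. They are aimed at switch versus eye-gaze within the cerebral palsy group, and at typically developing children versus children with cerebral palsy.

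The sentence also points elsewhere than secondary aim 2. It relates test results to secondary outcomes, whereas the aim asks what affects participation.

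At stake is the ability to see real associations in a small group that is hard to recruit. A non-significant table test could be read as no association when the method had little chance of finding one.

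**Working it through.** **Plan's own figure.** There is none for this analysis. The 80% power under Sample size calculations refers to equivalence between administration methods and does not bear on these associations.

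**Inputs from the article.** The tests are chi-squared or Fisher's exact; the test results are continuous scores; n is 40 or 38.

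**Assumptions (not in the article).** Two-sided 5% level; bivariate normal variables; both split at the median into a 2×2 table; true correlation r from 0.3 to 0.6.

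**Step 1: where the table tests reject.** With equal margins h = n/2 and a children high on both variables, chi-squared = n × ((2a − h)/h)².
- n=40, a=13: 40 × (6/20)² = 3.6, p=0.058, not rejected.
- n=40, a=14: 40 × (8/20)² = 6.4, p=0.011; Fisher p=0.026. Both reject.

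At n=40 the two tests therefore give the same decisions. Their actual type I error in simulation is 2.6%, not 5%. At n=38, uncorrected chi-squared already rejects at a=13 (38 × (7/19)² = 5.16, p=0.023), while Fisher's p there is 0.0502. They part company, with actual sizes of 5.1% and 0.8%.

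**Step 2: power with two quantitative variables** (60,000 simulated data sets per cell). Relative loss = 1 − (table power / Pearson power). For example, at n=40 and r=0.4: 1 − 0.278/0.743 = 63%.

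| r | Pearson, n=40 | Chi-squared or Fisher, n=40 | Loss | Pearson, n=38 | Chi-squared, n=38 | Loss | Fisher, n=38 | Loss |
|---|---|---|---|---|---|---|---|---|
| 0.3 | 0.480 | 0.156 | 68% | 0.458 | 0.221 | 52% | 0.073 | 84% |
| 0.4 | 0.743 | 0.278 | 63% | 0.716 | 0.361 | 50% | 0.147 | 79% |
| 0.5 | 0.923 | 0.451 | 51% | 0.908 | 0.538 | 41% | 0.278 | 69% |
| 0.6 | 0.989 | 0.654 | 34% | 0.985 | 0.728 | 26% | 0.462 | 53% |

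**Step 3: check that discreteness does not drive the n=40 result.** Replace the discrete table by the large-sample calculation: phi = (2/π) × arcsin(r), noncentrality = n × phi². At r=0.4, phi = 0.262 and noncentrality = 40 × 0.262² = 2.75, giving power 0.381 and a loss of 1 − 0.381/0.743 = 49%. Across r = 0.3, 0.4, 0.5 and 0.6 the loss is 52%, 49%, 39% and 26%. Part of the n=40 loss is thus discreteness; most of it is the categorising.

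**Step 4: a rank test in place of Pearson.** In a separate set of runs at n=40, Spearman power is 0.432, 0.686, 0.885 and 0.979, against 0.153, 0.273, 0.450 and 0.646 for the table. The loss is about 65%, 60%, 49% and 34%, so the result does not depend on a normal-theory comparator.

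**Step 5: a genuinely binary factor, 20 v 20, only the score split, n=40** (20,000 runs; d is the standardised mean difference).

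| d | t-test | Median-split table | Loss |
|---|---|---|---|
| 0.6 | 0.452 | 0.232 | 49% |
| 0.8 | 0.693 | 0.407 | 41% |
| 1.0 | 0.867 | 0.599 | 31% |
| 1.2 | 0.958 | 0.777 | 19% |

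**The case against.** **Not every variable is a score.** Completion and type of cerebral palsy are categorical, and the functional levels are ordered categories. A table test is reasonable for completion by type. This stands, and it limits the criticism to associations that involve a score, time or rating. It does not rescue the sentence, because the sentence concerns test results, which are scores.

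**The size of the loss is assumed.** The article specifies no median split, 2×2 table or effect size here. A reader might infer that most of the power is lost in general. The documents do not support that: the loss is below half for stronger correlations, for uncorrected chi-squared at n=38 with r of 0.5 or more, and for a binary factor. It exceeds half mainly for weak to moderate correlations at n=40, or with Fisher at n=38. The n=40 figures also compare a 5% test with one whose actual size is 2.6%.

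**Cut-points may be set elsewhere.** A reader might infer that they would be picked after seeing the data. Nothing in the article says so. Category definitions are commonly left to an analysis plan, so their absence is not part of this point. Even well-chosen, prespecified categories would discard information.

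**Secondary aim 2 may be covered.** A reader might infer that it has no analysis at all. That goes too far: the article does not define its secondary outcomes closely, the abstract mentions multiple regression, and participation read as completion would suit a table test against type. What stands is narrower: the sentence as worded makes test results one side of the association, while the aim concerns participation.

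**Conclusion.** The point holds as a mismatch between a stated method and the stated scale of the data. A table test is the only method named for associations in which one side is always a continuous score. The relative power loss is 34–68% at n=40 for two quantitative variables; at n=38 it is 26–52% with uncorrected chi-squared and 53–84% with Fisher; for a binary factor at n=40 it is 19–49%. These ranges rest on median splits, normal variables, r of 0.3 to 0.6 and d of 0.6 to 1.2, none of which the article gives. That the test discards information does not depend on these assumptions.

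This is a secondary analysis. It does not touch the equivalence, intraclass correlation or Bland–Altman hypotheses. The comparison of user experience between access methods is assigned to regression and does not depend on this sentence either.

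**What to change.** Replace the closing sentence of Data processing and analysis with methods matched to the variables:

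- **Score, time or rating against another such variable:** Spearman correlation, or linear or ordinal regression, with functional levels entered as ordered predictors.
- **Categorical factor against a score:** a rank or ANOVA-type test.
- **Two genuinely categorical variables,** such as completion by type of cerebral palsy: chi-squared or Fisher's exact test.
- **Secondary aim 2:** name completion and completion time as the outcomes, and relate them to type, functional level, pain, age and socio-demographic position. With about 40 children, keep to few predictors per model, and use an exact or penalised logistic model for completion if events are sparse.

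The cost is a few lines of text. No new data, visits or participants are needed, because every variable is already collected in the form these methods use.
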